## Methods/Design

### Study Design

PREDICT is a prospective, population-based cohort study of four patient care strategies provided by regional EMS services to patients with chest pain and suspected ischemia.

1. 3-lead PHECG and transported to the nearest receiving ED who were not eligible for bypass based on transport time.

2. 3-lead PHECG and transported to the nearest receiving ED who were eligible for bypass based on transport time, if 12 lead PHECG was possible.

3. 12-lead PHECG and prehospital notification transported to the nearest receiving ED who were not eligible for bypass to a PCI center based on transport time.

4. 12-lead PHECG with prehospital notification and eligible for bypassing the nearest receiving ED with transport to a PCI center.

Bypass eligibility was based on transport distance of patients from their pick-up location to PCI center and the cut-off point was 60 kilometres.

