### Analysis Plan

The primary outcome, and treatment time intervals, will be analyzed with one-way ANOVA and subsequent pair-wise multiple comparison procedures across the four treatment strategies. Different covariates (Table 3) will be analyzed using multiple linear regressions and they will be introduced into the model and evaluated as potential confounders. Variables will be retained if they have had an effect of 5% or greater on the coefficients for door-to-reperfusion time. Survival at 30 days and one year for STEMI patients will be analyzed as a binary outcome (Chi square) and as a survival analysis. Covariates that may affect survival will be analyzed with a Cox PH Regression Model. Adverse event rates will be analyzed with a Chi square analysis or a Fisher's exact test.

**Table 3 T3:** Analysis Plan - List of Covariates

1. Presence of cardiac catheterization lab in the primary destination hospital with the ability to perform 24-7 emergent primary angioplasty;
2. Fully affiliated teaching hospital;
3. Is the ED on Time Consideration (TC) or deferral from ambulances based on workload of acutely ill or injured patients?
4. Is the ED on Consideration (C) or deferral from ambulances based on workload?
5. Weekday;
6. Weekend;
7. Time of day in 8 hour intervals (08:00-16:00, 16:00-24:00, 24:00-08:00);
8. Age (as a continuous variable);
9. Sex;
10. History of MI;
11. History of CABG;
12. History of angioplasty;
13. Location of STEMI (anterior, posterior, inferior);
14. Off load delay (minutes);
15. PCA or PCI or bypass surgery.

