Economic outcomes will be analyzed using decision analysis supplemented with probabilistic sensitivity analysis in a simulation model. Direct costs will be estimated for each of the four treatment strategies. Door-to-reperfusion times and mortality will be available at the patient level, which will allow for the calculation of averages as well as variability estimates for analysis of uncertainty. Average cost and effectiveness (time-to-reperfusion interval and life years) will be calculated and if one treatment strategy is found to be superior (i.e. cost savings with survival benefits), and then these results will be reported in a cost consequence format. If the superior strategy is found to involve cost and outcome trade-offs (i.e. cost increasing with survival benefits), then incremental cost-effectiveness, as measured through additional cost per reduction in time-to-reperfusion interval and additional cost per life year gained, will be calculated.

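### The economic verdict rests on average outcomes per strategy with no stated link to the adjusted analyses, although strategy is set by region and distance

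*Protocol article*

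**What the plan says.** The Study Design section describes an observational comparison: "PREDICT is a prospective, population-based cohort study of four patient care strategies provided by regional EMS services". Within it, the bypass groups are formed by geography: "Bypass eligibility was based on transport distance of patients from their pick-up location to PCI center and the cut-off point was 60 kilometres".

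The Analysis Plan treats survival in two sentences. The first begins "Survival at 30 days and one year for STEMI patients will be analyzed as a binary outcome (Chi square" and goes on to name a survival analysis as well. The second is "Covariates that may affect survival will be analyzed with a Cox PH Regression Model". For door-to-reperfusion time it plans multiple linear regression on the covariates of Table 3, with this selection rule: "Variables will be retained if they have had an effect of 5% or greater on the coefficients for door-to-reperfusion time". No such rule is given for survival.

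The economic part of the Analysis Plan names its inputs: "Door-to-reperfusion times and mortality will be available at the patient level, which will allow for the calculation of averages as well as variability estimates". The verdict is then built on those averages: "Average cost and effectiveness (time-to-reperfusion interval and life years) will be calculated". If one strategy saves cost and improves survival, it is reported as superior in a cost-consequence format. If there is a trade-off, the additional cost per reduction in time to reperfusion and per life year gained is computed. The analysis is a decision model with probabilistic sensitivity analysis. The Economic Outcomes section adds that life expectancy gains from reduced mortality take the age and gender of subjects into account.

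**The concern.** Patients are not exchangeable between the four strategies by design. The regions range from 0.6 to 574 persons per square kilometre (Setting), and the protocol itself expects geography to matter: it lists a subgroup analysis for geographical bias and another for rural against urban settings. Any difference in age or cardiac history that follows geography would appear in crude mortality, and in crude times, as if the strategy had caused it.

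The protocol plans covariate models for both survival and time. The economic text, however, refers to averages and mentions neither model. Followed as written, it would turn a raw mortality gap into life years and then into a label of superior or a cost per life year, with no adjustment in between. This matters because the authors hope that the superior strategy will be adopted across all communities and that the results will inform budget decisions.

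**Working it through.** **What can be reproduced.** The protocol gives no mortality rate, survival effect or economic figure. Its only calculation, Table 2, concerns the primary outcome. It reproduces as a two-sided comparison of two proportions with continuity correction (402, 185 and 107 per arm, against 402, 185 and 106 printed) and has no bearing on this point. All mortality figures below are therefore assumptions.

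**The planned analyses side by side.**

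| Analysis | Covariates stated? | Strategy stated as a term? | Said to feed the economic model? |
|---|---|---|---|
| Chi-square, 30 days and one year | No | Yes, implicitly, as the grouping | No |
| Cox model | Yes | No | No |
| Linear regression for reperfusion time | Yes (Table 3) | Not outright | No |
| Averages of times and mortality | No | Yes, by strategy | Yes |

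Only the last row is named as the input to the verdict, and no adjustment is stated for it.

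**Illustration 1: an age difference and no strategy effect.** Assume 8% mortality in one group, a mean age 3 years higher in the other, and odds of death rising 6% to 8% per year of age.
- Baseline odds: 0.08 / 0.92 = 0.0870.
- At 6% per year: 1.06³ = 1.191; odds 0.0870 × 1.191 = 0.1036; risk 0.1036 / 1.1036 = 9.4%.
- At 8% per year: 1.08³ = 1.260; odds 0.0870 × 1.260 = 0.1095; risk 0.1095 / 1.1095 = 9.9%.
- Spurious gap: 1.4 to 1.9 points.
- At an assumed 10 life years per death averted: 0.014 × 10 = 0.14 to 0.019 × 10 = 0.19 life years per patient.

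**Illustration 2: two risk strata, again with no strategy effect.** Crude mortality is low-risk mortality × (1 − share) + high-risk mortality × share, where share is the high-risk share.
- Middle case (mortality 5% and 15%, shares 30% and 50%): 0.05 × 0.70 + 0.15 × 0.30 = 8.0%, against 0.05 × 0.50 + 0.15 × 0.50 = 10.0%. Gap 2.0 points.
- Smallest case tried (4% and 12%, shares 30% and 40%): 6.4% against 7.2%. Gap 0.8 points.
- Largest case tried (3% and 20%, shares 25% and 55%): 7.25% against 12.35%. Gap 5.1 points.

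**Set against sampling error.** With the planned 100 STEMI subjects per group, the standard error of a difference near 8% against 9.5% is √(0.08 × 0.92 / 100 + 0.095 × 0.905 / 100) = 0.040, or 4.0 points. The gap in illustration 1 is thus 1.4 / 4.0 = 0.35 to 1.9 / 4.0 = 0.48 standard errors. Over the cases in illustration 2, a two-group test would declare the gap significant only about 4% to 23% of the time. The economic rule as written has no significance test, so a gap of this size enters whether or not a test would flag it.

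**Why sensitivity analysis does not help.** Probabilistic sensitivity analysis draws each input from a distribution around its estimate. If the estimate is shifted by case mix, so is the centre of every draw. The spread reflects sampling error, and the shift remains.

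**The case against.** A reader might infer that survival is compared only by a crude chi-square. The text does not support that: the sentence naming the chi-square goes on to a survival analysis, and a Cox model with covariates follows. The chi-square is one of two planned analyses and is not named as the deciding one. Reporting crude and adjusted results together is normal in a cohort study.

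A reader might also infer that the adjusted result never reaches the economic verdict, or that the chi-square result feeds it. The protocol says neither. The stated inputs are averages of patient-level times and mortality, and that these are unadjusted is read from the absence of any link to the models. This is a condensed article, and a fuller plan may set out the model inputs.

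The size of the bias is also open to challenge. The protocol gives no age or comorbidity data by group, every mortality input is assumed, and in illustration 1 the gap is less than half a standard error. Table 3 already lists sensible baseline covariates, the subgroup analyses address geography, and age and gender enter the life expectancy step.

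These points limit the wording and the confidence in the size, but they do not remove the problem. The article states its decision rule, and the rule uses averages. Age and gender are there to convert mortality reductions into life expectancy; they are not said to adjust the mortality difference itself. Subgroup analyses do not change what enters the decision model. The Cox sentence leaves open whether strategy is in the model and whether that model leads.

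**Conclusion.** The point holds for the economic verdict. As written, superiority or cost-effectiveness is decided on average cost, time to reperfusion and life years per strategy in groups formed by region and distance, with no statement that adjusted estimates are used. If raw averages are used, case mix alone could produce an apparent mortality gap of about 1.4 to 1.9 points, or 0.14 to 0.19 life years per patient, under the assumed age difference; the two-stratum cases give 0.8 to 5.1 points. None of these inputs comes from the protocol, so the figures show plausible size and do not estimate the actual bias.

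For survival itself the criticism is narrower. An adjusted model is planned, but its role and the place of strategy in it are not stated. The outcomes concerned are secondary, and the change is worth making because the economic result is meant to guide policy.

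**What to change.** - State that the inferential comparison of survival is the planned Cox model, with strategy as a term and a prespecified set of baseline covariates from Table 3: age, sex, history of MI, CABG or angioplasty, and STEMI location. Leave out items that arise after the strategy has acted, such as whether PCA, PCI or bypass surgery was performed.
- Keep the crude 30-day and one-year percentages and the chi-square as description.
- State that the decision model takes adjusted or standardised mortality and time-to-reperfusion estimates for each strategy, with their uncertainty, in place of raw averages. The probabilistic sensitivity analysis then draws from those.

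**Cost.** The covariates are already to be collected, so this is a little more analysis. The real limit is the number of deaths: at the assumed 8%, 0.08 × 400 = 32. The covariates named above need about 10 coefficients (3 for strategy, 1 each for age, sex, MI, CABG and angioplasty, 2 for three STEMI locations), or 32 / 10 = 3.2 deaths per coefficient. The set must therefore be shortened or the model penalised. Adjustment also covers only what is measured; differences tied to region or distance may remain and should be acknowledged beside the economic result.

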### A Priori Subgroup Analysis

• Rural vs. urban settings and academic vs non academic destination hospitals

• Geographical bias subgroup analysis comparing all non PCI capable sites for distance from PCI site;

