### Access to Interventions

The rate of reperfusion strategy utilization across groups including fibrinolysis, percutaneous coronary angiography and intervention, coronary artery bypass surgery, bypass to PCI centre directly vs. transfer from a non PCI centre.

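### Two of the a priori subgroup analyses are defined by the hospital the patient reaches, which bypass itself changes

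*Protocol article*

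**What the plan says.** The A Priori Subgroup Analysis section of the protocol article has two items. The first is "Rural vs. urban settings and academic vs non academic destination hospitals". The second is "Geographical bias subgroup analysis comparing all non PCI capable sites for distance from PCI site". Neither names an outcome or a strategy contrast.

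The Study Design section defines the strategies that these subgroups would be applied to. Strategy 4 is "12-lead PHECG with prehospital notification and eligible for bypassing the nearest receiving ED with transport to a PCI center". Its counterpart with a 3-lead ECG, strategy 2, is "3-lead PHECG and transported to the nearest receiving ED who were eligible for bypass based on transport time, if 12 lead PHECG was possible". Strategies 1 and 3 are the 3-lead and 12-lead groups out of bypass range. The same section gives the geographic rule: "Bypass eligibility was based on transport distance of patients from their pick-up location to PCI center and the cut-off point was 60 kilometres".

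Table 3 in the Analysis Plan lists the covariates. Neither distance nor rurality is among them. The closest item is again a property of the hospital reached: "Presence of cardiac catheterization lab in the primary destination hospital with the ability to perform 24-7 emergent primary angioplasty".

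**The concern.** A subgroup meant to show whether a strategy effect differs between kinds of patient or place should rest on something fixed before the strategy acts. Destination hospital is not fixed in that sense here, because bypass changes the destination. Splitting by it conditions on a consequence of the strategy, and a larger sample does not cure that.

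The geographical-bias analysis has a related difficulty. Bypass is one of the two system factors that the study was set up to evaluate, and the contrast that depends on it is the one for which distance matters most. An analysis limited to hospitals without PCI leaves out the patients who received the bypass.

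The Discussion says the results are meant to inform policy and budget decisions. A reader could take a reassuring geographical-bias result as covering bypass. The same reader could take the non-academic row as describing communities served by non-academic hospitals. Neither reading would be justified.

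**Working it through.** No figure in the plan bears on how the subgroups are defined, so the check is mainly a comparison of sections.

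**1. Who is in the geographical-bias analysis.** It is restricted to hospitals without PCI capability.
- Strategies 1 and 3: taken to the nearest ED and out of bypass range, so present wherever that ED lacks PCI.
- Strategy 2: taken to the nearest ED, so present wherever that ED lacks PCI.
- Strategy 4, bypassed: at a PCI centre, so absent by definition.
- Strategy 4, eligible but not in fact bypassed: may be present.

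The recruitment goal is 100 STEMI patients per group. If a fraction f of strategy 4 is actually bypassed (f is not given in the documents), at most 100 × (1 − f) can remain:

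| f (assumed) | Strategy 4 patients left, at most | Bypassed patients left |
|---|---|---|
| 0.5 | 50 | 0 |
| 0.7 | 30 | 0 |
| 0.9 | 10 | 0 |
| 1.0 | 0 | 0 |

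The last column is zero at every f. Any strategy 4 patients left are those for whom bypass did not happen, a selected remainder.

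**2. Who is in each academic stratum.** Under strategy 2 the destination is the nearest ED, so the stratum reflects where the patient was picked up. Under strategy 4 the destination of a bypassed patient is the PCI centre. Whenever the PCI centre and the bypassed ED differ in academic status, that patient changes stratum, while a strategy 2 patient picked up at the same place does not. If the PCI centre is academic, the strategy 4 patients left in the non-academic stratum are those not bypassed, and the academic stratum gains the bypassed ones. If the PCI centre is non-academic and the bypassed ED academic, the movement runs the other way. Only if bypass never crosses that line does the split stay comparable, and the documents do not say that it never does.

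**3. Whether the plan handles distance elsewhere.** The 60 km rule puts strategies 2 and 4 in one band and 1 and 3 in the other, so 4 v 2 and 3 v 1 are each within a band. That control is coarse: patients in one band may lie anywhere from 0 to 60 km from the PCI centre, and those in the other at any distance beyond it. The Discussion describes 3-lead provision as a matter of region or county, so 4 v 2 is largely a comparison between regions, whose distance distributions may differ within the band. Table 3 has no distance term, and its catheterization-laboratory item cannot stand in for one because it too describes the destination.

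**4. Whether a better variable exists.** The distance from pick-up location to PCI centre, which the plan already uses for eligibility, is settled before the destination is chosen and cannot be altered by bypass. The subgroup section does not use it.

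**The case against.** The strongest defence is that the second item answers a different question. For a patient who starts at a hospital without PCI, the distance to the PCI site affects the transfer interval. That interval is one of the listed treatment times, and the Access to Interventions section lists "bypass to PCI centre directly vs. transfer from a non PCI centre" as a comparison. Bypassed patients have no place in that question. This stands: the comparison is coherent for transferred patients. It does not stand as a check for geographical bias across the four strategies.

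It can also be said that geography is handled elsewhere, by the 60 km split and by the rural v urban subgroup. That stands in part. The item is the only analysis labelled for geographical bias, but it is not the only place where geography enters. A reader might infer that rural v urban has the same defect. The text does not support this: it speaks of settings, the Setting section uses such terms for areas by population density, and only the academic split is clearly tied to the destination.

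A reader might further infer that the academic subgroup would reverse the sign of the bypass effect. The documents do not support that either. A reversal needs the strategy 4 patients who were not bypassed to do worse than strategy 2 patients, for which there are no data. It also needs PCI centres to be the academic sites, which is not stated; Table 3 lists teaching affiliation and catheterization capability separately. If every strategy 4 patient went to an academic PCI centre, the non-academic stratum would hold no strategy 4 patients at all and there would be no estimate to mislead.

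Lastly, much subgroup detail belongs in an analysis plan. The objection here is not to missing detail but to a definition that the article fixes.

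**Conclusion.** The point holds for two of the listed analyses. The academic v non-academic subgroup is defined by a variable that bypass changes, so strategies 4 and 2 are not comparable populations within a stratum wherever bypass moves a patient between academic and non-academic hospitals. The geographical-bias analysis contains no bypassed patient, whatever fraction is bypassed, and cannot show whether the bypass contrast is affected by distance.

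The number of strategy 4 patients lost depends on an unstated bypass fraction, and the direction and size of any distortion cannot be determined from the documents. The conclusion rests on reading sites and destination hospitals as the hospital the patient was taken to, which is their plain sense. The primary comparison across the four strategies does not use these subgroups and is not affected. This is a worthwhile and inexpensive correction, not a flaw that threatens the main result.

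**What to change.** In the A Priori Subgroup Analysis section:

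- Define the academic v non-academic subgroup by the receiving ED nearest the pick-up location, for all four strategies, in place of the destination hospital.
- Run the geographical-bias analysis on the distance from pick-up location to PCI centre, over all patients in the four strategies, within 4 v 2 and within 3 v 1.
- Keep the comparison of hospitals without PCI by distance, if wanted, as a separate question about transferred patients, and label it so.

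The form of the distance term and any interaction test can be left to the statistical analysis plan. The rural v urban item needs no change on this ground.

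The cost is a change of wording plus a small amount of data work. The nearest ED may have to be derived from the pick-up location, and the variable lists, which are in additional files not shown, should be checked to confirm that the pick-up location or its distance is stored. The change does not make the subgroups larger: Table 2 asks for 106 per arm to detect 20 points between whole groups and about 100 are planned, so subgroup results will be descriptive under either definition.

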### Ethical Considerations and Human Subjects Protection

PREDICT is an observational, prospective non-interventional study based on review of routinely collected source data and as such meets the requirements for minimal risk research[38-40]. Approval by 47 research ethics boards/committees covering 71 hospitals will be sought to launch the study.

## Discussion

There is a lack of a comprehensive dataset for Acute Coronary Syndrome (ACS) patients, which includes the prehospital component of care[3]. We anticipate that this study will bridge this gap, providing valuable information on processes of care and the benefits of different prehospital treatment strategies. We have planned to address four threats to protocol compliance and internal validity; 1) ethics approval and privacy requirements from 47 research ethics boards/committees covering 71 hospitals, 2) temporal bias of comparison induced by delays to implementation across sites, 3) data guardian training and oversight of timeliness and quality, and 4) technological advances that may outpace the study and affect recruitment.

This trial involves rural and urban centres and this means that many research ethics boards will need to review this protocol and our request for waiver of consent. We anticipate that rural and small community hospitals will struggle with the request for waiver of consent and the privacy issues associated with chart abstraction, acquisition of personal information enabling telephone follow up at 30 days and at one year. Our strategy will be to obtain approval from all the academic centres first and enclose a copy of their approval with submission to the smaller centres. In addition we have established a data sharing agreement template that has the approval of the administration and legal advisors of the 18 academic and community hospitals in our largest metropolitan area. This agreement has been used successfully in other trials and we hope this will facilitate reaching agreement more quickly with hospitals that have not been involved with research previously. And, finally our investigators will be on call to the research ethics board to participate in the discussion at the time of review. Many small hospital boards request this level of participation by the investigator. We have found in the past that this strategy is helpful in minimizing correspondence back and forth between the research team and the ethics board and reduces time to approval.

We recognize the limitations and challenges that might affect the study's successful implementation and generalizability such as time and spatial challenges. If at all possible, the study should be launched in all centres at the same time. However prior to launching, each PREDICT participating site will need to confer with stakeholders to ensure capture of all cases, procurement of all source documents, optimization of timely data flow, and training of data abstractors. For some centres this preparation and initiation phase will be more elaborative and time consuming then for the others based on volume and existing infrastructure and prior research experience. To address these potential delays we will target the sites we anticipate the REB will be slower to approve the protocol, with follow up calls and offers to complete additional information or speak by teleconference to the board or to the ethics board chair to facilitate understanding and a timely response to queries. We will engage the medical directors in all the sites to ensure the flow of documentation allows for timely data entry and to encourage them to identify and support a high quality data guardian for their site. This engagement will take the form of web based reports of site performance and patient outcomes available 24-7 that enable medical directors to see their data and compare to the aggregate site data. To date most medical directors do not have access to performance or outcome data and we hope providing this accessibility will speed implementation and timely quality data. We anticipate these interventions may be sufficient to allow all sites to participate concurrently and limit the bias related to temporal changes in practices during the trial.

By protocol, the data is collected by trained data guardians in all the sites and since almost all the data guardians are geographically remote from the central research coordinating centre the quality of data may suffer and poise a threat to internal validity. In total there are 10 data guardians abstracting prehospital data and 16 data guardians abstracting inhospital data. To encourage uniformity in data collection and to provide oversight and ensure quality, a number of interventions are planned. All data guardians will be individually trained by one of the investigators (VR). The web based data entry system has built in data definitions and abstraction instructions which are accessible through point and click technology on the variable name at the time of data entry. The abstraction instructions are listed hierarchically ensuring that the data is abstracted from the best source if at all possible. All variables are subject to error and logic checks across other variables and across forms (inhospital and prehospital) which are applied at the time of completion and the case will not close without reconciliation of all the error. Web conferences are conducted for all data guardians to highlight changes to the data set structure, upgrades to the software and discuss difficult variables identified by the data guardians or by the investigators. Data reports to test uniformity are planned and will be discussed at weekly team meetings of the research staff and investigator steering meetings.

Technological advances may outpace the study. Some regions/counties that provide 3-lead ECG in the prehospital setting are not currently considering the change in technology, while other areas are in the planning or transitional stages. Any change from 3-lead to 12-lead in a participating site will compromise recruitment rates and regional comparisons. If this happens an additional 3-lead site with similar geographic and demographic characteristics will be recruited and retrospective data collection will occur to permit concurrent comparisons. In anticipation of this threat to the protocol we have engaged each of the EMS medical directors in the decision to participate. The window of the trial has been confirmed to correspond to the planned changes in the services considering a change.

We have planned a prospective cohort study to compare outcomes across two different prehospital interventions (12-lead and 3-lead) and two system changes (transfer to closest hospital versus bypass closest hospital to transfer directly to a PCI capable hospital) that do not lend themselves to evaluation by a randomized controlled trial. We anticipate there will be challenges related to ethical and privacy, oversight of data guardian abstraction, timeliness of implementation, and technological advances. We hope that this evaluation may be helpful to those involved in developing and enhancing multidisciplinary systems of care including EMS services to advance local care of patients with STEMI and to inform policy decision making and evidence based budgetary decisions that ultimately will affect care across the Province.

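### Temporal bias from uneven site launch is named as a threat, but calendar date appears in neither the primary comparison nor the Table 3 covariates

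*Protocol article*

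**What the plan says.** The Discussion names four threats to protocol compliance and internal validity. The second is "temporal bias of comparison induced by delays to implementation across sites".

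On launch timing, the same section says: "If at all possible, the study should be launched in all centres at the same time". It then says: "For some centres this preparation and initiation phase will be more elaborative and time consuming then for the others". Ethics submissions are sequenced: the strategy is to "obtain approval from all the academic centres first and enclose a copy of their approval with submission to the smaller centres". The countermeasures are follow-up with slow ethics boards, engagement of medical directors and web-based site reports. The stated expectation is that these steps may be enough for all sites to run concurrently and "limit the bias related to temporal changes in practices during the trial".

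Technology change is treated separately: "Any change from 3-lead to 12-lead in a participating site will compromise recruitment rates and regional comparisons". If a site converts, a comparable 3-lead site is to be recruited with retrospective data, and the trial window has been checked against planned changes.

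In the Analysis Plan, the primary outcome and the time intervals are compared by one-way ANOVA with pairwise follow-up. For confounders, "Different covariates (Table 3) will be analyzed using multiple linear regressions", and a variable stays in if it moves the door-to-reperfusion coefficients by at least 5%. Table 3 has 15 items. Those that concern time are weekday, weekend and time of day in 8-hour blocks.

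**The concern.** The article identifies a bias and then sets out an analysis that cannot remove it. A one-way ANOVA carries no covariates. The adjusted models draw on a list that covers daily and weekly cycles but not the months-to-years scale on which practice changes. The 5% rule can act only on variables that are entered, so it cannot bring calendar time in.

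The route from site delay to group difference is plausible. The Discussion describes 3-lead and 12-lead capability as belonging to regions or counties, so a lag between services can become a lag between strategy groups. If door-to-reperfusion performance is also improving, the later-enrolling strategy gains credit for the calendar. The study is meant to inform provincial policy and budgets, so a drift of a few points credited to a prehospital strategy would matter.

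**Working it through.** **1. Match each threat to its remedy.**

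- Late launch: ethics-board follow-up, medical-director engagement and web reports (Discussion). No analytic step is stated.
- Conversion from 3-lead to 12-lead: a replacement 3-lead site with retrospective data, and a matched trial window (Discussion). These are design measures, but conversion triggers the replacement and planned technology change sets the window. Neither deals with late launch.
- Calendar time in the analysis: absent from the ANOVA and from all 15 items of Table 3.

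**2. Reproduce the plan's own scale.** Table 2 gives 402, 185 and 106 per arm for differences of 10, 15 and 20 points from 37.4%, with alpha 0.05 and 80% power. The two-sided two-proportion formula is

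n = [1.96 √(2p̄(1−p̄)) + 0.8416 √(p₁(1−p₁) + p₂(1−p₂))]² / d²,

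and the continuity correction gives n′ = (n/4)[1 + √(1 + 4/(nd))]². This returns 402, 185 and 107. Table 2 therefore reproduces to within one subject per arm, and 20 points is a fair yardstick for a recruitment goal of 100 per group.

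**3. Size of the drift.** Spurious difference = trend (points per year) × gap in mean enrolment date between two strategy groups (years). Both inputs are assumptions, because the documents give neither.

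**4. Effect on one pairwise test.** Take n = 100 per group, no true strategy effect, p₁ = 0.374 and p₂ = 0.374 + b, where b is the spurious difference. The two-sided z-test rejects with probability Φ((b − c)/SE₁) + Φ((−b − c)/SE₁), where c = 1.96 √(2p̄(1−p̄)/n) and SE₁ = √([p₁(1−p₁) + p₂(1−p₂)]/n).

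For b = 0.10: p̄ = 0.424, c = 1.96 × 0.0699 = 0.137 and SE₁ = 0.0695. The first term is Φ(−0.53) and the second is negligible, giving 29.8%.

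| Assumed trend (points/yr) | Assumed gap (yr) | Spurious difference (points) | Share of 20 points | False-positive rate |
|---|---|---|---|---|
| 0, or any | any, or 0 | 0 | 0% | 5.0% |
| 2 | 0.5 | 1 | 5% | 5.2% |
| 5 | 0.5 | 2.5 | 12.5% | 6.5% |
| 5 | 1 | 5 | 25% | 11.1% |
| 10 | 1 | 10 | 50% | 29.8% |

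The last column is for a single comparison at 0.05, before any multiple-comparison correction, and uses a two-proportion test as a stand-in for the planned ANOVA.

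**The case against.** The strongest reply is that the article describes a risk being managed, not a planned stagger. It aims for simultaneous launch and expects its measures may achieve it. If they do, the bias is near zero. That stands, and it is why the range must start at zero.

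Second, late approval need not mean late episodes. The study reviews routinely collected records, so a slow board might delay abstraction without shifting which patients are included. The documents do not settle this, so it limits the concern without removing it.

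Third, Table 3 is not declared closed, and a fuller analysis plan could add a date term. But the article does state a covariate list, and that list has short-cycle time items without the time scale of the bias it names. An analyst who follows this text leaves that bias unadjusted.

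Three stronger readings are tempting, and the documents do not support them:

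- A reader might infer that the plan has only operational protection against any temporal bias. The replacement site and the matched window are design-level protection against technology change. The gap concerns late launch.
- A reader might infer that rural and small hospitals, and hence late starters, fall mainly in the groups not eligible for bypass. No passage says so. Eligibility depends on each patient's distance from the PCI centre (60 km cut-off), so one service can supply both distance groups. Nor do the documents say whether 3-lead or 12-lead services start later, so the direction of any bias is unknown.
- A reader might take a bias of some definite share of the design difference as established. It is not. Each strategy group may pool several of the 14 services, which would dilute a delay at any one site.

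**Conclusion.** The point holds in conditional form. The article names temporal bias from uneven launch as a threat to internal validity, offers only operational steps against it, and specifies a primary comparison and covariate list without calendar date. Bias arises only if two things occur together: strategy groups enrol at different mean dates, and target attainment changes over time.

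Its size cannot be derived from the documents. On assumed inputs it runs from zero to about 10 points, or up to half of the 20-point difference in Table 2. At the low end (2 points a year, half a year apart) it is negligible. At the high end, a nominal 5% pairwise test would reject about 30% of the time with no strategy effect. The change is worth making because it is cheap and answers a threat the authors raise themselves.

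**What to change.** Add episode date to Table 3, as calendar quarter or as a smooth term in months since study start. Keep it in the adjusted models for the primary outcome and the treatment time intervals regardless of the 5% retention rule. As a sensitivity analysis, repeat the primary comparison using only the period in which all four groups were enrolling. Report the distribution of episode dates by strategy, so that readers can see the overlap.

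No new data should be needed: survival is counted from the episode date, and weekday and weekend are derived from it. The cost is a few degrees of freedom in the models and some loss of precision in the restricted analysis. Where a strategy and a calendar period do not overlap, adjustment cannot separate them. The restricted analysis is informative only if a common enrolment period exists. If there is none, that should be stated as a limitation of the comparison.
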